### Outcome Measures and Assessment Procedures

#### Baseline Assessment

Baseline assessments were completed within three months of inclusion in the study, approximately two weeks prior to the first intervention session and prior to randomisation. Baseline and post intervention assessments took between 60 to 90 minutes to complete (including the provision of short breaks), with a two hour session allocated for the more detailed 12 and 24 month follow ups. The assessments comprised a series of tests and questionnaires, and included the following:

#### Primary outcome measure

Cambridge Cognitive Screen (CAMCOG): This is the brief neuropsychological battery of the Cambridge Examination for Mental Disorders of the Elderly - Revised (CAMDEX-R) [18] that includes a range of objective cognitive tests. It provides sub-scale scores for a number of cognitive domains as well as a global score out of 105. It takes approximately 30 minutes to administer and is very effective at differentiating between people with and without dementia [19]. There is also evidence that CAMCOG scores are sensitive to change over time [20]. The CAMCOG is the primary outcome measure of this study.

#### Secondary Outcome Measures

California Verbal Learning Test-Second Edition (Standard and Alternate Forms) (CVLT-II) [21]: This is a 16-item word list task that measures verbal learning and memory. It yields scores on immediate and delayed recall as well as recognition. Provision of standard and alternate forms minimises practice effects and are being used to monitor change in memory functions. The CVLT-II was chosen as a secondary outcome measure because low scores on word list learning tasks are associated with progression to dementia [22].

The Symbol Search sub-test from the Wechsler Adult Intelligence Scale-Third Edition (WAIS-III) [23] yields a measure of perceptual processing speed. Participants are asked to indicate whether target symbols appear in a search group of symbols. There are 60 items consisting of paired groups of symbols and the individual has 120 seconds to complete as many items as possible. Prior research has found that CA is associated with lower rates of decline on measures assessing processing ability such as perceptual speed and working memory [24], supporting the use of Symbol Search and Digit Span (see below) as an additional secondary outcome of interest.

The Digit Span sub-test from the WAIS-III [23] comprises forward and backward span components assessing individuals' auditory immediate attention and working memory. The examinee listens to a series of digits given orally by the examiner and then repeats the digits either in a forward or reverse sequence. Testing is discontinued after failure on the two trials of any series.

The Trail Making Test (TMT) [25] has two parts and measures complex visual scanning, motor speed and mental agility. In Part A the participant draws lines to connect consecutively numbered circles. Part B requires the participant to connect a sequence of numbered and lettered circles, alternating between the two sequences. The tests are timed, with participants instructed to complete the sequencing as quickly as possible.

The Controlled Word Association Test (COWAT) [25] consists of three word naming trials, with the letters FAS employed. Participants are asked to say as many words as they can think of that begin with the given letter of the alphabet, excluding proper nouns, numbers and the same word with a different suffix. A minute is given for each letter trial and performance is used as an indicator of executive functioning.

PHQ-9: We used the PHQ-9 total score, as previously described, to monitor changes in mood throughout the trial.

Leisure Activity and Frequency Questionnaire [4]: This seven-item questionnaire assesses the frequency of participation in a variety of mentally stimulating leisure activities. Given the relationship identified between leisure activity and cognitive decline [24], the aforementioned questionnaire was chosen to identify the effects that the individual's level of activity over the course of the study may have on their rate of cognitive decline.

Participants also rated their level of engagement in *physical activity *[26]. They were asked to indicate how much time they spent, over a week, taking part in vigorous and non-vigorous activity. An additional questionnaire was also added to identify the nature and quality of the participants' *social relationships *[27].

The Memory Functioning Questionnaire (MFQ) [28]: The MFQ is a 64-item questionnaire evaluating self-perception of everyday memory functioning. It was used at baseline and across follow-up assessments to determine the influence of the intervention on perceived level of memory ability.

The Quality of Life in Alzheimer's Disease (QoL-AD) [29]: This is a 13-item questionnaire completed by the participant assessing their perception of their quality of life across a number of different domains.

Participants were also asked to provide specific details regarding their educational and occupational background.

The assessment battery described above was repeated immediately after the intervention (please see details below) and again after 12 and 24 months (please see table 1). The 12 and 24 month follow-up assessments were undertaken relative to the baseline testing and also included the additional measures administered at the "Clinic Screen".

**Table 1 T1:** Outline of the assessments and timelines of the PACE trial.

*Assessment Tool*	Telephone Screen	Clinical Screen	Baseline (0 weeks)	Post-Intervention (12 weeks)	12 months (52 weeks)	24 months (104 weeks)
TICS-M	X					

PHQ-9	X	X	X	X	X	X

CERAD		X			X	X

MMSE		X			X	X

AUDIT		X			X	X

SAILS		X			X	X

MHQ		X			X	X

CAMCOG			X	X	X	X

CVLT-II			X	X	X	X

Digit Span			X	X	X	X

Symbol Search			X	X	X	X

TMT			X	X	X	X

COWAT			X	X	X	X

LAQ			X	X	X	X

PAQ			X	X	X	X

SNSQ			X	X	X	X

MFQ			X	X	X	X

QOL-AD			X	X	X	X

The X indicates at which point of the trial the respective assessments took place. Follow-up times relate to baseline testing.

A booster telephone call took place at 24 weeks, with a face to face booster at 52 weeks.

TICS-M = The Modified Telephone Interview for Cognitive Status; PHQ-9 = Patient Health Questionnaire - Nine Item; CERAD = Consortium to Establish a Registry for Alzheimer's Disease; MMSE = Mini Mental State Examination; AUDIT = Alcohol Use Disorders Identification Test; SAILS = Structured Assessment of Independent Living Skills; MHQ = Medical Health Questionnaire; CAMCOG = Cambridge Cognitive Examination; CVLT-II = California Verbal Learning Test - Second Edition; TMT = Trail Making Tests; COWAT = Controlled Oral Word Association Test; LAQ = Leisure Activity Questionnaire; PAQ = Physical Activity Questionnaire; SNSQ = Social Network Satisfaction Questionnaire; MFQ = Memory Functioning Questionnaire; QOL-AD = Quality of Life in Alzheimer's Disease.

#### Biological Sample and DNA Collection

We also asked participants to donate a blood or saliva sample to determine the influence of common biochemical (e.g., high plasma homocysteine) and genetic factors (e.g., apolipoprotein E4 genotype) on participants' response to the intervention. The samples are being collected and processed by the Department of Clinical Pathology and Biochemistry at the RPH where they are currently stored at -80°C. All material has been batched and will only be processed at the end of the trial.

### Intervention

The interventions (both CA and education) consisted of a five-week group activity run by a qualified Neuropsychologist at the WACHA. The CA and control education groups were exposed to the same length of intervention, social interaction and contact with the program coordinator. Both the CA and educational intervention were manualised and delivered in a structured way, and all sessions (220) were audio-taped for subsequent fidelity assessment. Forty four of these sessions were randomly selected and transcribed. An independent rater used a specially devised scale to evaluate session content for consistency of concepts and issues raised across sessions according to a pre-defined criteria.

Research assistants (RAs) blinded to group allocation conducted all assessments. RAs were provided with strict instructions to avoid any potential opportunity for disclosure regarding intervention participation. The intention is that RAs undertaking data collection will be asked to guess the group membership of participants at the end of the study. This will be done to determine the effectiveness of the blinding procedures that were put in place for this project. A brief summary of each intervention is provided below.

#### CA Group

Each group consisted of 6-9 participants who took part in 90-minute sessions twice a week for five weeks (10 sessions in total). Session One introduced the nature of the program and developed familiarity within the group, with personal introductions and sharing of background information/experiences. Sessions Two and Three focussed on the cognitive domains of attention, processing speed and executive functions, how these domains change as people age and the influence they have on memory abilities. Participants were advised about strategies to manage cognitive decline associated with these domains, including a number of practical exercises. Sessions Four to Seven primarily focused on memory, with the aim of defining the processes involved in learning and retaining new information. These sessions provided participants with strategies and techniques to manage memory dysfunction. There was regular opportunity for supervised practice of such techniques in all sessions. Session Eight reviewed age associated language difficulties and aimed to provide participants with ways to manage word finding difficulties, as well as affording opportunity for undertaking language-based exercise activities. Sessions Nine to Ten were used to practice and review the previously presented material and recommended strategies, and to discuss any difficulties managing the strategies/techniques previously presented.

As part of the intervention, all participants received a folder containing the slides of each session, and copies of all completed activities.

#### Education Group

Each educational group consisted of 6 to 9 participants who took part in 90-minute sessions twice a week for five weeks (10 sessions in total). Session One followed the same format described for the CA group. Session Two covered the topic of memory functioning and dementia, aiming to provide a broad overview of how these issues can affect older people. Session Three reviewed the health benefits associated with physical activity and ways to incorporate physical activity into daily lifestyle. Sessions Four and Five were devoted to defining stress and depression as well as reviewing the cause, effects and management of these conditions. Session Six outlined changes in sleep associated with ageing and the management of sleep disturbance. In sessions Seven to Nine, focus was placed on issues of retirement including expectations, lifestyle changes, volunteer activities, cultural/societal implications of ageing and travelling. Session Ten reviewed the content of material covered in the previous weeks and provided opportunity for discussion of any questions/issues arising from the presented topics. In contrast to the CA group, there was no emphasis on skill development or the promotion of mentally stimulating activities and sessions had a greater level of mental passivity. However, as in the CA group, there was opportunity for group discussion and interaction and participants were provided with a folder containing the slides of each session.

#### Booster Sessions

All participants received a fifteen-minute "booster" telephone call six months after the baseline assessment to review and discuss the topics presented at the group sessions. Thirty minutes of additional exercise material was posted to participants in the CA group for completion prior to the booster call and served as the basis for discussion during the telephone contact. After the 12-month assessment a face-to-face group 1-hour booster session was offered to both intervention groups. This session was used to review the practical aspects of the CA and educational programs.

### Randomisation

After the baseline assessment, participants were randomly allocated to either the CA or control education interventions according to a random list of numbers generated by computer. Randomisation was undertaken in random blocks of 12 to 18, with six to nine individuals allocated to each group. The allocation list was handled by an independent investigator ([name]) who had no contact with study participants and was not involved in the supervision of staff responsible for the collection of data. The allocation table was then passed on to the investigator running the intervention (MV), who invited eligible participants to join the relevant groups. Research assistants undertaking the follow-up assessments remained blinded to group allocation.

### Sample Size and Power Calculation

At present there is no reliable data for calculating the sample size of the proposed trial. Currently available data suggests that older people living in the community lose 1.6 points per year on the CAMCOG [30]. Factoring in a possible 20% loss to follow up, with 64 people in each group we will have 80% power to detect a between-groups difference of 1.5 points on the CAMCOG. This assumes a decline that is twice as large in the educational compared with the cognitive intervention group, and although statistically this may be associated with moderate effect size (0.5), it is the minimum difference that one would consider clinically significant.

### Analysis of the Data

Changes in the CAMCOG score from baseline are the primary outcome of interest in the study. We will model these changes at 3 time points: 12 weeks (immediately after the intervention comes to an end), 52 and 104 weeks. We will use mixed effects models to analyse the data. This approach will enable us to take into account the cognitive performance of participants at baseline, as well as the intra-person correlation generated from repeated measures. Intention-to-treat analyses will be based on the use of imputation by chain equations (ICE), which will precede the use of the mixed-effects model.

We accept that participation in the cognitively non-specific educational intervention is likely to have an effect on the performance of participants. However, to ensure continued participation of the control group we deemed it crucial to provide some form of intervention or potentially face differential drop out, with the control group participants withdrawing because of lack of engagement in the study. We will model changes over time for both groups and this will enable us to determine the effect of both interventions (as well as the sustainability of this effect over 24 months) on cognitive performance.

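### Both arms are delivered in about 22 session groups, but the sample size makes no allowance for clustering and the described mixed model names only within-person correlation; the 80% power is conditional on no within-group correlation

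*Protocol article*

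**What the plan says.** **Delivery.** The CA Group section states: "Each group consisted of 6-9 participants who took part in 90-minute sessions twice a week for five weeks". The Education Group section gives the same group size and schedule. The Intervention section reports that "all sessions (220) were audio-taped for subsequent fidelity assessment".

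**Group formation.** Session groups come directly from the randomisation. The Randomisation section says: "Randomisation was undertaken in random blocks of 12 to 18, with six to nine individuals allocated to each group". Each block therefore supplies one group to each arm.

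**Sample size.** The Sample Size and Power Calculation section states that, after allowing for 20% loss, "with 64 people in each group we will have 80% power to detect a between-groups difference of 1.5 points on the CAMCOG". It describes this as a "moderate effect size (0.5)". It gives no ICC, design effect or number of groups.

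**Analysis.** The Analysis of the Data section plans mixed effects models after imputation by chained equations. It says this approach accounts for baseline performance "as well as the intra-person correlation generated from repeated measures". Session group is not mentioned.

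**The concern.** Randomising individuals does not remove correlation that arises after allocation. Members of a session group share the same peers, discussions and calendar period for ten sessions. Session One is meant to build familiarity within the group, and the education arm also has group discussion. If this makes members' outcomes more alike, each arm carries less information than 64 independent people would.

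Two things are then at stake. The 80% power for a 1.5-point difference, which the article calls the smallest clinically significant one, would be overstated. And a model with only person-level correlation would give a standard error for the CA-education contrast that is too small, with a false-positive rate above 5%.

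**Working it through.** **Inputs from the article.** 64 completers per arm; difference 1.5 points; effect size 0.5, so the implied SD is 1.5/0.5 = 3.0; 20% loss; 160 enrolled; groups of 6-9; 10 sessions per group; 220 sessions.

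**Assumptions.** The article states neither alpha nor ICC. I take a two-sided 5% level (a one-sided test would need only 50 per arm, which does not match) and ICCs of 0.01, 0.05 and 0.10. I also take the 220 sessions to be the ten-session courses.

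**1. Reproduce the plan's figure.** The normal approximation gives 63 per arm. Noncentral-t power at 64 per arm, with noncentrality 0.5 × √(64/2) = 2.83 and 126 degrees of freedom, is 80.1%. Then 64/0.8 = 80 per arm, or 160 in total. The figure reproduces exactly, with no allowance for clustering.

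**2. Number and size of groups.** 220/10 = 22 groups, about 11 per arm. Mean size is 160/22 = 7.3 enrolled, which lies within 6-9, and 128/22 = 5.8 completers.

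**3. Effect of a positive ICC.** The design effect is DE = 1 + (5.82 − 1) × ICC. The effective number per arm is 64/DE, and the true standard error is √DE times the independent-participant one. Power is noncentral t at effect size 0.5. If groups are ignored, type I error is 2 × [1 − Φ(1.96/√DE)].

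| ICC | DE | Effective n per arm | √DE | Power, person-level df | Difference detectable at 80% | Type I error if groups ignored, at most |
|---|---|---|---|---|---|---|
| 0 | 1.00 | 64.0 | 1.00 | 80.1% | 1.50 | 5.0% |
| 0.01 | 1.05 | 61.1 | 1.02 | 78% | 1.53 | 5.6% |
| 0.05 | 1.24 | 51.6 | 1.11 | 71% | 1.67 | 7.9% |
| 0.10 | 1.48 | 43.2 | 1.22 | 63% | 1.82 | 10.7% |

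The type I figures are upper bounds. They treat the whole ICC as specific to the session group, whereas correlation shared by a whole block largely cancels, because each block supplies one group to each arm.

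**4. Degrees of freedom, a separate matter.** Testing the contrast against 22 − 2 = 20 degrees of freedom lowers power to about 77% (detectable difference 1.56 points) even at ICC 0. With clustering added, power is about 75%, 68% and 60% for the three ICCs. If blocks are also modelled, with one group per arm in each of 11 blocks, about 10 degrees of freedom remain between groups. This loss should not be read as the effect of correlation.

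**The case against.** **The ICC may be close to zero.** This is the strongest objection, and much of it stands. Allocation is individual, so the groups were not pre-existing clusters. Sessions were manualised and checked for fidelity. One neuropsychologist apparently ran both arms, which would remove facilitator differences. The outcome is an objective test battery given by blinded assessors. At ICC 0 with person-level degrees of freedom the stated power holds, and at 0.01 the loss is about two percentage points. A reader might infer that the power is certainly missed and the standard errors certainly too small. The documents do not support that, because both depend on a positive ICC that they do not give.

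**The model text is silent, not exclusive.** Mixed effects models can include a group term, and a condensed article may leave the random-effects structure to an analysis plan that is not shown. It would therefore be wrong to say that the plan rules such a term out. What stands is that the article says which correlation the model handles and names only one. The sample size is fixed in the article, and an unseen plan cannot change how the 80% was obtained.

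**The planned model may be more efficient than the t-test.** If baseline adjustment removed residual variance from the quantity powered (assumed correlation 0.3-0.4), unclustered power would be 84-86%. Conversely, an SD of 3.5 instead of 3.0 would give 67%. Both are possible and the article claims neither. They show that clustering is one of several uncertainties in the power figure.

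**Group contact should not be overstated.** The article does not call the groups closed; stable membership is inferred from the way blocks form groups. The face-to-face booster was offered after the 12-month assessment, so it cannot affect the 12- or 52-week outcomes.

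**Conclusion.** The point holds in conditional form. The stated 80% assumes zero correlation within session groups, an assumption the article neither states nor justifies, and the calculation has no margin to absorb a positive value. Across assumed ICCs of 0.01 to 0.10, power falls to between about 78% and 63%, and the difference detectable at 80% power rises from 1.50 to between 1.53 and 1.82 points. If the session group is left out of the analysis, the 5% type I error becomes at most 5.6% to 10.7%. Small-sample degrees of freedom lower power further.

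These figures rest on 22 groups, 5.8 completers per group, a two-sided 5% level and the implied SD of 3.0. The harm is minor at the low end of the range and material at 0.05 and above. Because the size depends on an unknown ICC that the delivery arrangements may keep small, this is a should-fix and not a demonstrated failure of the design.

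**What to change.** 1. Add a random intercept for session group (about 22 levels) above the person level in the CAMCOG mixed model, with Satterthwaite or Kenward-Roger degrees of freedom. If an analysis plan already does this, it is enough to show it.
2. Carry the session-group identifier into the chained-equations imputation, so that the imputed data keep any within-group correlation.
3. Restate power as conditional on the ICC over a stated range, for example 0 to 0.10, with degrees of freedom that match the fitted model: about 20 without a block term, about 10 if blocks are modelled too.

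The cost is one more random term in a model already planned and a less favourable power statement. No extra participants are needed. Group membership should be recoverable from the allocation table, and the final endpoint was expected only in December 2010, so the term can be fixed before the final outcome is known.

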**Methods/Design:**

The study will recruit 160 community-dwelling men and women aged 65 years of age or over with mild cognitive impairment (MCI). Participants will be randomly allocated to two treatment groups: non-specific education and cognitive activity. The intervention will consist of ten 90-minute sessions delivered twice per week over a period of five weeks. The primary outcome measure of the study is the change from baseline in the total score on the Cambridge Cognitive Score (CAMCOG). Secondary outcomes of interest include changes in memory, attention, executive functions, mood and quality of life. Primary endpoints will be collected 12, 52 and 104 weeks after the baseline assessment.

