## Background

The World's population is ageing rapidly and so is the frequency of age-related disorders. Dementia is one of the most frequent mental health disorders of older people and a leading cause of years of life lost due to disability [1]. Mild Cognitive Impairment (MCI) in old age is considered an important clinical state potentially predictive of future cognitive decline. The term MCI has been used to describe a heterogeneous group of older adults, who, whilst not fulfilling diagnostic criteria for dementia, demonstrate cognitive abilities at a level below what is considered normal for their age. Cognitive deficits may be apparent across unitary or multiple domains though the person continues to maintain a high level of functional independence [2]. Whilst this diagnostic group is at increased risk for conversion to dementia, a substantial number of individuals remain stable or even return to normal levels of functioning with time [3].

There is increasing evidence that the onset of dementia can be delayed by targeting relevant risk factors. In older adults, frequent participation in mentally stimulating leisure activities has been associated with stronger cognitive abilities (such as memory) and reduced risk of dementia [4,5]. The idea that mentally stimulating activity can influence cognitive processes is akin to the "use it or lose it" adage [6]. Few randomised controlled studies have explored this notion and critical evaluation of the research on this topic reveals a number of methodological limitations. These include the specific nature of some of the participant cohorts, the tests used to measure cognitive functioning, and the complexity associated with identifying and defining a broad range of leisure activities with regard to type and degree of cognitive stimulation (see [6] for a review).

Cognition-focused interventions (cognitive training, cognitive rehabilitation and cognitive stimulation) attempt to make use of intact domains to help maintain cognition and prevent/delay decline. These techniques have also been employed to increase functional independence and reduce caregiver burden (see [7] for a review).

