Similar to mentally stimulating leisure activities, cognitive stimulation (CS) is a type of intervention that emphasises the benefits of group activities focussing on education, discussion and debate, and problem solving. In contrast, cognitive rehabilitation (CR) can be tailored towards an individual's needs, with consideration given to specific areas of impairment and an emphasis on improving everyday functioning. Another commonly used strategy is cognitive training (CT), which aims to provide the individual with a set of standardised tasks that they repeatedly perform. CT using specifically designed computer programs has become a burgeoning business and is generating increasing scientific interest.

Collectively, the research in this area has revealed that older adults (with and without dementia) show modest gains across areas related to the target intervention, and improvements on subjective measures assessing aspects of mood and quality of life have also been observed [8]. However, there is a paucity of randomised controlled trials in this area, limiting conclusions that can be drawn from existing data.

We have designed a single-blind, randomised controlled trial of an intervention that draws on methods of cognition-focussed approaches, selected with regard to suitability for older adults with MCI, and combined into a package considered interesting, engaging and acceptable to this group. The primary focus of this research is to determine whether a structured program of cognitive activity (CA) can decrease the rate of cognitive decline amongst older adults with MCI over 24 months. We hypothesize that participants allocated to the CA group will experience less cognitive decline than older adults randomised to a control education intervention.

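### With two randomised arms that both receive a programme, modelling change in each arm cannot give the effect of each programme; only the CA-minus-education difference is identified

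*Protocol article*

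**What the plan says.** The Abstract (Methods/Design) describes two arms: "Participants will be randomly allocated to two treatment groups: non-specific education and cognitive activity". The Intervention and Randomisation sections agree. Both arms attend ten group sessions, and no untreated, wait-list or usual-care arm is described.

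The hypothesis at the end of the Background is between-arm: "We hypothesize that participants allocated to the CA group will experience less cognitive decline than older adults randomised to a control education intervention". The Sample Size and Power Calculation section is also between-arm, with 64 per group, 80% power and a difference of 1.5 CAMCOG points.

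The second paragraph of Analysis of the Data goes further. It concedes that the control is not inert: "We accept that participation in the cognitively non-specific educational intervention is likely to have an effect on the performance of participants". It gives retention as the reason for that choice: "to ensure continued participation of the control group we deemed it crucial to provide some form of intervention". It then offers modelling as the answer: "We will model changes over time for both groups and this will enable us to determine the effect of both interventions", including whether that effect is sustained over 24 months.

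**The concern.** The sentence claims something that the design cannot deliver. Randomisation supports one causal contrast, CA against education. The separate effect of each programme would need a reference for what happens to similar people who receive neither, and the analysis section names none.

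The article itself identifies other causes of change in CAMCOG scores:

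- **Repeat testing.** Table 1 schedules the CAMCOG at 0, 12, 52 and 104 weeks. For the CVLT-II the article notes: "Provision of standard and alternate forms minimises practice effects". It mentions no alternate form for the CAMCOG. Practice gains would look like benefit.
- **Natural decline.** The sample size section cites data that "older people living in the community lose 1.6 points per year on the CAMCOG". Decline would look like harm, or would hide a benefit.
- **Spontaneous reversion.** The Background says of people with MCI that "a substantial number of individuals remain stable or even return to normal levels of functioning with time". This may add apparent benefit.

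The stake is greatest if the two arms do not differ. The sentence would then leave room to report that both programmes work (if both arms improve) or that neither does (if both decline). The data would support neither conclusion.

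**Working it through.** **1. The plan's own figures reproduce.** Inputs from the sample size section: difference 1.5 points, effect size 0.5, power 80%, 20% loss. Alpha is not stated; two-sided 5% is assumed.

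- Implied SD = 1.5 / 0.5 = 3.0 points.
- A two-sample t-test at effect size 0.5 needs 63.8, so 64 per arm. Power at 64 per arm is 0.801.
- Allowing for loss: 64 / (1 − 0.20) = 80 per arm, 160 in total, as stated.

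The between-arm design is internally consistent, and this point leaves it alone.

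**2. What two arms identify.** Let D be the mean change with no programme (practice + natural decline + reversion), and let E_CA and E_ED be the programme effects.

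- Mean change, CA arm = D + E_CA
- Mean change, education arm = D + E_ED
- Difference = E_CA − E_ED

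There are two observed means and three unknowns. D cancels in the difference, but E_CA and E_ED cannot be recovered separately. Suppose, hypothetically, that both arms fall by 0.5 points at 52 weeks. That fits each of the following equally well:

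| D | E_CA = E_ED | Reading |
|---|---|---|
| −1.6 (the cited yearly decline) | −0.5 + 1.6 = +1.1 | both help |
| −0.5 | 0 | neither does anything |
| 0 (practice offsets decline) | −0.5 | both harm |

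A longitudinal model of the two arms cannot choose between these rows.

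**3. Illustration of size.** Assume a one-sample t-test of mean change in one arm, n = 64, two-sided 5%, and no programme effect. The SE is SD/√64, which is 3.0/8 = 0.375 for SD 3.0 and 6.0/8 = 0.75 for SD 6.0. Probability of a significant within-arm change:

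| Drift, points (either direction) | SD 3.0 | SD 6.0 |
|---|---|---|
| 0.5 (assumed) | 0.26 | 0.10 |
| 1.0 (assumed) | 0.75 | 0.26 |
| 1.5 (assumed) | 0.98 | 0.50 |
| 1.6 (cited yearly decline) | 0.99 | 0.56 |
| 3.2 (2 × 1.6, if linear over 104 weeks) | about 1.00 | 0.99 |

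The same drift in both arms leaves the between-arm test at its nominal 5%.

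**The case against.** The best defence is that the trial's main inference is sound. The hypothesis and the power calculation are both between-arm, the mixed model can supply that contrast at each visit, and common drift drops out of it. That stands in full. A reader might infer that the primary comparison is biased or underpowered for this reason; the document does not support that.

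Three further objections also limit the point:

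- **No decision rule is stated.** A reader might infer that within-arm significance will decide efficacy. The analysis section sets no within-arm test or threshold. It claims only that modelling change will reveal each effect, so the test in the illustration is supplied here.
- **Regression to the mean is a tempting explanation but a weak one.** Participants were selected on the TICS-M and on CERAD tasks with the MMSE, not on the CAMCOG, whose baseline was a separate later assessment. It is at most a minor contributor. The Background remark about return to normal functioning concerns the clinical course of MCI and is not evidence of this artefact.
- **The plan expects decline in both arms.** It is therefore unlikely to mistake decline for harm. Decline also works against a false claim of benefit and may offset practice gains. Nor should the 1.6-point yearly decline be weighed against the 1.5-point target, since common decline cancels from the target.

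It could also be said that the sentence refers only to the between-arm comparison. Its context makes that unlikely: it follows directly on the concession that education may itself affect performance, and it speaks of the effect of both programmes.

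**Conclusion.** The sentence is wrong as written and should be fixed. The trial can estimate the CA-minus-education difference in CAMCOG change, and how that difference lasts. It cannot estimate either programme's own effect, or the sustainability of that effect. This follows from the two-arm design, so no analysis of these two arms alone, in an unseen analysis plan or elsewhere, could make the claim true.

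The fault is confined to this additional claim; the primary hypothesis, the 64 per arm and the 80% power stand. The conclusion does not depend on the illustrated percentages. Those rest on three assumptions: that the SD of 3.0, back-calculated from a tentative effect size in a section that admits to having no reliable data, applies to within-person change; a two-sided 5% level; and drift sizes which, apart from 1.6 and its doubling, are not from the document.

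**What to change.** Replace the sentence in Analysis of the Data with a statement of three things:

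1. Efficacy and its sustainability are judged from the CA-minus-education differences in CAMCOG change at 12, 52 and 104 weeks.
2. Changes within each arm are reported descriptively, with confidence intervals and without causal wording.
3. The effect of either programme against no intervention cannot be estimated in this trial.

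The remarks on the control being active and on retention can stay, since they explain why the third statement is needed.

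The cost is one reworded sentence. No new data are needed, and the sample size stays at 160. The investigators give up a claim that the design could not support.
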